### **4.4 Sample size calculation**

If a less optimistic scenario is assumed, with 25% deterioration (transfer to ICU or death on ward or in ICU) in the control arm and 10% in the intervention group, the power calculation is as follows: 25% vs 10% → 100 subjects per group → 200 subjects total → 10% dropout → 224 subjects needed. An interim analysis is planned with stopping rule according to O'Brien Fleming, for which no adjustment of the sample size is needed. After 50 patients in each arm

## **5. TREATMENT OF SUBJECTS**

For 8 consecutive days, once daily ¼ Potassium Iodide 65 mg tablet. Total iodine dosage during the treatment course amounts to 130 mg. After 8 days, a significant reduction in SARS-CoV-2 virus titers in nasal and throat swabs is observed [26].

### **5.1 Investigational product/treatment**

Potassium Iodide 65 mg tablet

### **5.2 Use of co-intervention (if applicable)**

Patients receive the same standard treatment as other patients with a COVID-19 infection. There are no restrictions on the use of other medication.

### **5.3 Escape medication (if applicable)**

Not applicable

## **6. INVESTIGATIONAL PRODUCT**

### **6.1 Name and description of investigational product(s)**

Potassium Iodide 65 mg tablet

### **6.2 Summary of findings from non-clinical studies**

No known studies

### **6.3 Summary of findings from clinical studies**

No known studies

### **6.4 Summary of known and potential risks and benefits**

The likelihood of side effects is derived from the listings in the pharmacotherapeutic compass for Potassium Iodide 65 mg tablets. The side effects listed there are relatively mild and in principle transient. In rare cases, in patients with pre-existing thyroid disorders, thyrotoxicosis may occur. Temporary medicinal treatment may then be necessary to correct thyroid dysfunction. However, this is not expected since thyroid disorders or medication related to thyroid dysfunction are exclusion criteria. Previous studies show that administering relatively high doses of iodine is safe [10,11,12].

### **6.5 Description and justification of route of administration and dosage**

Oral administration for 8 days, once daily ¼ Potassium Iodide 65 mg tablet is minimally burdensome for the patient and easy to administer by nursing staff. Furthermore, the tablets are very inexpensive (€0.01 per tablet according to the pharmacotherapeutic compass). Various in vitro studies and animal model research have identified different required concentrations to achieve virus inactivation. These studies focused particularly on viruses with an envelope, as the SARS-CoV-2 virus also has one. Required concentrations for envelope virus inactivation range between 10 µM and 80 µM iodine [2, 3, 7, 21, 22].

To estimate the required dosage, the following assumptions were made:

- The iodine concentration in alveolar fluid is 20 times higher than in serum [2]. This concentration difference can be achieved through active transport of iodine to the lumen via Sodium-Iodide Symporters in the mucosa.
- For an average weight of 80 kg, the amount of body water is approximately 50 liters.
- Of the administered daily ¼ Potassium Iodide 65 mg tablet, 100% (16.5 mg) is absorbed.
- The half-life of iodine measured in alveolar lung fluid after a single Potassium Iodide administration in animal models is approximately 24 hours [2]. After a single intake of Potassium Iodide, the iodine level in serum returns to baseline within 24 to 48 hours [24].
- Molar mass of Potassium is 40 g and molar mass of Iodine is 127 g, totaling 167 g. Therefore, in 16.5 mg Potassium Iodide, there is  $(127/167) \times 16.5 \text{ mg} = 12.5 \text{ mg}$  Iodine. This corresponds to  $(0.0125/127) = 98 \text{ µmol}$  iodine.
- With a volume of 50 liters of body water, the concentration of iodine is  $98/50 = 2 \text{ µM}$
- Of the total amount of iodine in the body, half (6 mg to 14 mg) is stored in the thyroid [23]. The other half is assumed to be peripherally available. So in the body itself, 6 to 14 mg iodine is available in 50 liters of body water. This corresponds to  $6/50 = 0.12 \text{ mg}$  ( $0.94 \text{ µmol}$ ) and  $14/50 = 0.28 \text{ mg}$  ( $2.2 \text{ µmol}$ ) per liter.
- The concentration calculation in serum is then the sum of existing iodine in serum + the added iodine:  $0.94 + 2 = 2.94 \text{ µM}$  and  $2.2 + 2 = 4.2 \text{ µM}$ .
- The iodine concentration in alveolar fluid is 20 times higher than in serum. So the calculated extremes of iodine concentration in serum of 2.94 µM and 4.2 µM correspond to  $2.94 \times 20 = 58.8 \text{ µM}$  and  $4.2 \times 20 = 84 \text{ µM}$  in alveolar lung fluid.
- Literature indicates that the required dosages for inactivation of envelope viruses lie between 10 µM and 80 µM.
- As our calculation shows, our daily dosage of ¼ Potassium Iodide 65 mg tablet falls within the range of required iodine concentrations for inactivation of envelope viruses at alveolar lung fluid level.
- The iodine administration lasts 8 days because a clear reduction in SARS-CoV-2 virus titers is only seen after a week [25]. Additionally, we administer iodine not only for its antiviral properties but also for its antioxidant effect, which is needed to address the free radicals generated during a possible cytokine storm. Therefore, we have chosen a treatment duration of 8 days. The total dosage of the course then amounts to 130 mg Potassium Iodide.

## 6.6 Dosages, dosage modifications and method of administration

For 8 consecutive days, once daily ¼ Potassium Iodide 65 mg tablet. Distributions are registered by the nurse in the electronic prescribing system of the hospital's EHR.

## 6.7 Preparation and labelling of Investigational Medicinal Product

This concerns an available medicinal product that will be provided via the hospital pharmacy.

## **6.8 Drug accountability**

Potassium Iodide will only be provided during the hospital stay. The prescription will be recorded in the electronic prescribing system of the hospital's EHR.

## **7. NON-INVESTIGATIONAL PRODUCT**

### **7.1 Name and description of non-investigational product(s)**

Not applicable

### **7.2 Summary of findings from non-clinical studies**

Not applicable

### **7.3 Summary of findings from clinical studies**

Not applicable

### **7.4 Summary of known and potential risks and benefits**

Not applicable

### **7.5 Description and justification of route of administration and dosage**

Not applicable

### **7.6 Dosages, dosage modifications and method of administration**

Not applicable

## **7.7 Preparation and labelling of Non-Investigational Medicinal Product**

Not applicable

## **7.8 Drug accountability**

Not applicable

# **8. METHODS**

## **8.1 Study parameters/endpoints**

### **8.1.1 Main study parameter/endpoint**

Primary endpoint: clinically relevant deterioration. Deterioration is defined as:

- From baseline on general ward to ICU
- From baseline on general ward and death
- From baseline in ICU and death

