## SUMMARY

**Rationale:** Iodine has germicidal properties and contributes to the defense mechanism against pathogens. In addition, iodine has anti-inflammatory and immune-modulating properties that may have a beneficial effect in the treatment of COVID-19 infections. This leads to our hypothesis that iodine is effective in the treatment of COVID-19 disease.

**Objective:** To demonstrate that iodine treatment has a beneficial effect on the course of COVID-19 disease. Beneficial effect is defined as a reduced risk of deterioration, such as transfer from a regular ward to the ICU, death in the regular ward, or death in the ICU.

**Study design:** Open-label randomized trial with a control group.

**Study population:** All patients aged 18 years and older who are admitted to the hospital and test positive for SARS-CoV-2 infection will be recruited for the study. Patients must be mentally competent and able to read the patient information sheet and sign the informed consent form.

**Intervention:** Patients in the intervention group will receive, for 8 consecutive days, once daily, ¼ Potassium Iodide 65 mg tablet. The control group will receive no supplement and no placebo.

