**Main study parameters/endpoints:**

Primary endpoint: clinically relevant deterioration. Deterioration is defined as:

1. From baseline on regular ward to ICU
2. From baseline on regular ward and death
3. From baseline in ICU and death

**Secondary endpoint:** total number of days of hospital admission and total number of deaths.

**Nature and extent of the burden and risks associated with participation, benefit and group relatedness:** When a patient is randomized and placed in the treatment group, a beneficial effect on the course of the COVID-19 infection is to be expected. The patient must then take ¼ Potassium Iodide 65 mg tablet once daily for 8 consecutive days. The risk, given the exclusion criteria, is very limited and in principle temporary.

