### **3. STUDY DESIGN**

Open-label randomized clinical trial with control group.

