## **8.2 Randomisation, blinding and treatment allocation**

Randomisation via Research Manager

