#### **11.2 Recruitment and consent**

Patients will be recruited by nursing staff, physician assistant in training, or attending physician. Consent will be requested by the investigator.

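### The only non-fatal primary event is an ICU transfer with no objective criterion in an open-label trial, so a transfer-driven difference could partly reflect knowledge of the arm

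*Protocol*

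**What the plan says.** Section 8.1.1 gives three primary components: "From baseline on general ward to ICU", death from a ward baseline, and "From baseline in ICU and death". The Summary and section 2 list the same three. Section 10.1 expresses the endpoint as numbers of transfers and numbers of deaths. No section attaches a physiological or organ-support criterion to the transfer.

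On blinding, section 3 reads "Open-label randomized clinical trial with control group" and the Summary adds "The control group will receive no supplement and no placebo". Section 8.2, whose title covers blinding, says only "Randomisation via Research Manager". Section 6.6 says "Distributions are registered by the nurse in the electronic prescribing system of the hospital's EHR", and section 11.2 says "Patients will be recruited by nursing staff, physician assistant in training, or attending physician". The burden-and-benefit paragraph of the Summary tells the reader that for a treated patient "a beneficial effect on the course of the COVID-19 infection is to be expected", while section 6.3 reports no known clinical studies.

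Section 10 tests the composite by log-rank with Cox regression and analyses death alone as a secondary endpoint by the same methods. Section 10.4 plans one interim look at 50 per arm, with a futility rule and an efficacy boundary of p<0.0054.

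**The concern.** As defined, the transfer component is a decision and not a state of the patient. A precautionary move and a move for ventilation count the same. Whoever makes the decision is not shielded from the allocation by anything in the protocol, and the protocol states an expectation of benefit. If iodine patients were kept on the ward a little more readily than controls, that difference would pass directly into the primary log-rank test. Section 8.1.3 lists oxygen saturation at admission only, so no planned variable documents the patient's condition at the time of transfer. A difference consisting mainly of transfers would then be hard to interpret.

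**Working it through.** **Inputs from the protocol.** Section 4.4: 25% control and 10% iodine event rates, 100 per group, 10% dropout, 224 in total. Significance level and power are not stated there.

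**Reproducing the sample size.** Two proportions, two-sided 5%, 80% power, no continuity correction:

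n = [1.96·√(2·0.175·0.825) + 0.84·√(0.25·0.75 + 0.10·0.90)]² / 0.15² = 99.5, so 100 per arm. Dropout: 100/0.9 = 111.1, so 112 per arm and 224 in total. This matches, so two-sided 5% is used below. At the planned rates the trial expects 25 + 10 = 35 events.

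**Assumptions for the bias check.** None of these is in the protocol.
- Iodine has no effect, and the true rate is 25% in both arms.
- A share f of primary events is ICU transfers. The protocol gives no split, so f = 40% to 80%.
- A fraction q of iodine-arm transfers is permanently withheld, and those patients have no later primary event.
- A two-proportion test stands in for the log-rank test.

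**Formula.** The observed iodine rate is p₂ = 0.25·(1 − f·q), against p₁ = 0.25. With d = p₁ − p₂, p̄ the mean of the two rates, s₀ = √(2p̄(1−p̄)/100) and s₁ = √((p₁(1−p₁)+p₂(1−p₂))/100), the rejection probability is Φ((d − 1.96s₀)/s₁) + Φ((−d − 1.96s₀)/s₁).

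Example, f = 0.8 and q = 0.4: p₂ = 0.25·(1 − 0.32) = 0.17, d = 0.08, s₀ = 0.0576, s₁ = 0.0573. The first term is Φ(−0.574) = 0.283 and the second is negligible.

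| Transfer share f | q = 20% | q = 30% | q = 40% |
|---|---|---|---|
| 40% | 6.3% | 7.9% | 10.3% |
| 60% | 7.9% | 11.8% | 17.5% |
| 80% | 10.3% | 17.5% | 28.3% |

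Without bias the figure is 5%.

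**In counts.** Against 25/100 control events, 14/100 in the iodine arm gives p = 0.0496 (uncorrected chi-square). Eleven transfers not made would be enough.

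**With the interim rule of 10.4.** Section 10.4 does not say how the sample size is recalculated. Assume observed rates at 50 per arm, 80% power, two-sided 5%, interim p<0.0054 and final p<0.0492. Simulated chance of a significant result at f = 80%:

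| Rule applied | q = 20% | q = 30% | q = 40% |
|---|---|---|---|
| Both futility limbs | about 4% | about 7% | about 12% |
| Only the 5-point limb | about 9% | about 16% | about 27% |

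With both limbs and no bias the chance is about 2%, so the relative inflation remains although the absolute risk is lower.

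**The case against.** **No contradiction in the text.** The endpoint is worded consistently throughout, an open-label design is not in itself an error, and an analysis plan that is not shown could add sensitivity analyses. This stands in part. However, an analysis plan cannot supply a criterion that the definition lacks, or data at transfer that were not recorded.

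**The size is soft.** At a 40% transfer share and 20% withheld, the error is 6.3%, close to nominal. Patients who enter from the ICU can contribute only deaths, which lowers the transfer share. A transfer that is merely delayed, or a patient who later dies on the ward, still counts as an event, so permanent deletion overstates the effect of delay. Section 10.4 would also stop many such trials. All of this stands, and it is why only a range can be given.

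**There are objective elements already.** Two of the three components are deaths, death alone has its own prespecified analysis, and 10.1 names transfers and deaths separately. This stands. It does not close the gap: every death from either baseline is itself a primary event, so deaths cannot outnumber patients with a primary event, of whom about 35 are expected at the planned rates.

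**Organ support is also started by unblinded clinicians.** True. A criterion based on it reduces the bias but does not remove it, and making it the primary endpoint would cost events that the trial can hardly spare.

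**Stronger readings a reader might infer.** One is that staff belief alone would produce a positive trial. The documents do not support that: they do not say who decides on transfer, the stated expectation of benefit is not an instruction about transfers, and a significant result becomes the likely outcome only with a large shift. Another is that the trial has no objective check at all. The death-alone analysis contradicts that.

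**Conclusion.** The point holds as a moderate weakness in the endpoint definition that should be corrected. An unblinded trial has a discretionary event as its only non-fatal primary component, with no criterion, no blinded adjudication and no planned record of the patient's state at transfer. That the deciding staff know the arm is very probable but inferred. Under the stated assumptions, the false-positive probability is about 6% to 28% before the interim rule, and about 4% to 12% at an 80% transfer share with both futility limbs applied. Where in that range the trial would fall depends on the transfer share and on staff behaviour, neither of which the protocol gives. The risk is that a transfer-driven difference could not be interpreted. It is not a demonstration that the result would be false.

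**What to change.** Keep any ICU transfer or death as the primary endpoint, and keep the sample size at 224. These changes concern only how events are recorded and analysed, not when a patient is moved.

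1. In section 8.1.1, record from the hospital record which organ support was started around each ICU transfer, within a stated time window.
2. In section 10, prespecify a sensitivity analysis that counts a transfer only when it is accompanied by charted organ support, together with all deaths. Give most weight to invasive ventilation, since the other supports are more open to discretion.
3. Report ICU transfer and death separately by arm.
4. State in advance that a benefit seen only in transfers without organ support will not be claimed as reduced deterioration.

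The cost is a few extra data fields and one extra analysis with fewer events and so lower power. Bias is reduced and made visible, but not removed.

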### **8.1.2 Secondary study parameters/endpoints (if applicable)**

Secondary endpoint:

- Total number of deaths
- Total number of days of hospital admission

If the subject has been admitted to the intensive care unit for part of a calendar day, this day counts as one full day of ICU admission. If the subject has been admitted partly to the ICU and partly to a general ward on a calendar day, this day counts as one full day of ICU admission. If the patient has been admitted to a general ward for part of a calendar day and has died or been discharged on that day, this day counts as one full day of general ward admission.

### **8.1.3 Other study parameters (if applicable)**

BSE, CRP, leukocytes, ferritin, oxygen saturation at admission, and temperature progression. These measurements and tests are performed as part of routine care.

## **8.2 Randomisation, blinding and treatment allocation**

Randomisation via Research Manager

## **8.3 Study procedures**

Review patient information form and sign informed consent. Inclusion period runs from July 1, 2020 to July 1, 2022.

## **8.4 Withdrawal of individual subjects**

Subjects may withdraw from the study at any time and for any reason, without consequences. The investigator may decide to withdraw a subject from the study for urgent medical reasons.

### **8.4.1 Specific criteria for withdrawal (if applicable)**

Not applicable

## **8.5 Replacement of individual subjects after withdrawal**

Dropout has been accounted for in the power calculation. No replacement will take place.

## **8.6 Follow-up of subjects withdrawn from treatment**

Follow-up lasts as long as the patient is hospitalized.

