## **10. STATISTICAL ANALYSIS**

The primary analysis of the endpoint “clinically relevant deterioration” is a Kaplan-Meier survival analysis with the duration being the number of days since study start. Study start is the calendar day on which the first dose of Potassium Iodide tablet is administered. The difference in transfer from general ward to ICU, death on general ward, or death in ICU will be tested using a log-rank test. Hazard ratios with 95% confidence intervals will also be calculated using Cox regression analysis.

Secondary analysis will be performed for death alone and total number of days of hospital admission. For this, a Kaplan-Meier with log-rank test and Cox regression analysis will be performed.

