### **10.1 Primary study parameter(s)**

Clinically relevant deterioration expressed as the number of patients transferred from a general ward to the ICU and the number of patients who die on the general ward or in the ICU.

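### With observation ending at discharge and no common horizon, the planned log-rank and Cox analyses by default compare in-hospital hazards, not the 25% and 10% the trial is sized on

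*Protocol*

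**What the plan says.** - **Follow-up.** Protocol section 8.6, headed for subjects withdrawn from treatment, states: "Follow-up lasts as long as the patient is hospitalized". No other section gives a follow-up period, a fixed assessment day or any contact after discharge.
- **Primary analysis.** Section 10 says the analysis of deterioration "is a Kaplan-Meier survival analysis with the duration being the number of days since study start". The combined outcome of ICU transfer, "death on general ward, or death in ICU will be tested using a log-rank test", and "Hazard ratios with 95% confidence intervals will also be calculated using Cox regression analysis".
- **Death and length of stay.** For these secondary analyses section 10 adds: "For this, a Kaplan-Meier with log-rank test and Cox regression analysis will be performed".
- **Sizing.** Section 4.4 works from two proportions, "with 25% deterioration (transfer to ICU or death on ward or in ICU) in the control arm and 10% in the intervention group", and arrives at "100 subjects per group → 200 subjects total → 10% dropout → 224 subjects needed".
- **Endpoint as reported.** Section 10.1 has "Clinically relevant deterioration expressed as the number of patients transferred from a general ward to the ICU", together with the number who die on the ward or in the ICU.
- **Expected effect on stay.** Section 11.4 lists a shorter admission among the possible benefits, and section 8.1.2 makes admission days a secondary endpoint.

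**The concern.** When observation stops at discharge, a time-to-event analysis needs a rule for patients discharged alive. The protocol gives none, and the usual default is to censor them on that day. Kaplan-Meier then treats them as though they carried the same future risk as patients still in hospital. But discharge alive largely means recovery. It competes with deterioration and is not a neutral loss to follow-up.

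Two things follow. The Kaplan-Meier curve no longer estimates the share of patients who deteriorate. And the log-rank and Cox analyses compare the cause-specific hazard, that is, the daily rate among those still in hospital. That rate moves with the length of stay as well as with the proportion deteriorating. If iodine speeds recovery, as the protocol hopes, a real fall in the proportion can be hidden. If it delays discharge, the contrast can be exaggerated. Deaths, too, are counted over a window whose length may differ between the arms.

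**Working it through.** **1. The plan's own figure.** Section 4.4 states neither alpha nor power. Taking two-sided 5%, 80% power and no continuity correction, with mean proportion (0.25 + 0.10)/2 = 0.175:

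n = [1.96·√(2·0.175·0.825) + 0.842·√(0.25·0.75 + 0.10·0.90)]² / 0.15² = (1.053 + 0.443)² / 0.0225 ≈ 99.5, so 100 per arm.

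100/0.9 gives 112 per arm and 224 in total. The stated size therefore reproduces as a comparison of two proportions.

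**2. What the planned test compares.** The protocol gives no length of stay, so these inputs are assumed: constant hazards and a control mean of 6 days to event or discharge.

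- Control: event hazard 0.25/6 = 0.0417 per day; discharge hazard 0.75/6 = 0.125 per day.
- Intervention: discharge hazard 0.125·r, where r is the discharge-rate ratio. To keep the true risk at 10%, the event hazard must be (0.10/0.90)·0.125·r = 0.0139·r.
- Cause-specific hazard ratio: 0.0139·r / 0.0417 = r/3.

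The true risks are 25% and 10% in every row, yet the hazard ratio moves with r. Simulated power, 100 per arm, whole days, two-sided 5%:

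| Discharge rate on iodine | Hazard ratio | Log-rank, censored at discharge | Log-rank, discharged carried event-free to day 28 |
|---|---|---|---|
| 1.5 times | 0.50 | 49% | 79% |
| unchanged | 0.33 | 87% | 83% |
| 0.75 times | 0.25 | 97% | 86% |

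Repeat runs differ by up to about 3 percentage points.

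**3. Equal risks, unequal stays.** Both arms at 25%, control mean stay 10 days (assumed).

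- 10 v 8 days: hazard ratio (0.25/8)/(0.25/10) = 1.25. The log-rank censored at discharge rejects about 11% of the time.
- 10 v 6 days: hazard ratio (0.25/6)/(0.25/10) = 1.67. It rejects about 40% of the time.

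With discharged patients carried to day 28, or with a test of two proportions, rejection is 5% to 7%. With the shorter stay on iodine, the censored analysis would suggest harm although the same proportion deteriorates.

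**4. Treatment only speeds discharge, 1.5-fold.** The intervention event hazard stays at 0.0417 and the discharge hazard becomes 0.1875, so the risk is 0.0417/(0.0417 + 0.1875) = 18%, down from 25%. The hazard ratio is 1.0. The log-rank censored at discharge rejects about 5% of the time, against about 20% with discharged patients carried forward.

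**5. The curve.** In the control arm with a 6-day mean, 1−KM(t) = 1 − exp(−0.25t/6) and the actual cumulative incidence is 0.25·(1 − exp(−t/6)).

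| Day | 1−KM | Cumulative incidence |
|---|---|---|
| 7 | 25% | 17% |
| 14 | 44% | 23% |

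With a 10-day mean, the day-14 values are 30% and 19%.

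**The case against.** - **The follow-up sentence stands under a heading for withdrawn subjects.** Correct, so applying it to all patients is an inference. It is, however, the only follow-up rule in the protocol, and section 6.8 provides the drug only during the hospital stay.
- **Nothing says that discharged patients are censored.** Also correct. A reader might infer that the protocol prescribes this, but it does not. Keeping them event-free to a common day would fit the wording of section 10, and a statistical analysis plan may do so. What stands is that the protocol fixes the test and the end of observation without the rule that would reconcile them with sections 4.4 and 10.1.
- **The endpoint is largely in-hospital.** Sections 4.4, 10 and 10.1 name ICU transfer and death on the ward or in the ICU; sections 2 and 8.1.1 do not say where death occurs. On the in-hospital reading, discharge is a fully observed competing event, and the log-rank is a valid test of the cause-specific hazard. That hazard is still not the 25% v 10% contrast.
- **Power need not suffer.** If the discharge rate is unchanged, the test censored at discharge is slightly stronger, 87% against 83%. A reader might infer that the trial is underpowered or biased towards no effect. The documents do not support that, because they give no size for any effect on discharge.
- **A dramatic curve proves little.** In the 6-day model, 1−KM at day 28 is 1 − exp(−28·0.25/6) = 69% for a true 25%. But only 100·exp(−28/6) = 0.9 of 100 patients would still be at risk, and day 28 is not the protocol's horizon. Days 7 and 14 are a fairer measure.

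**Conclusion.** The mismatch is real and should be fixed, though it does not by itself invalidate the trial. Read by default, sections 8.6 and 10 give a test of in-hospital hazards, while sections 4.4 and 10.1 speak of proportions and counts. For the same true 25% and 10%, power runs from about 49% to 97% according to discharge speed alone, against 79% to 86% with discharged patients kept at risk to day 28. With equal risks and unequal stays, the rejection rate can reach 11% or 40% in place of 5%.

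These figures rest on constant hazards and on assumed stays and discharge-rate ratios; none comes from the protocol. The direction is unknown. Faster discharge, which section 11.4 anticipates, is the case that dilutes a true benefit. The overstatement by 1−KM does not depend on any treatment effect on discharge. The sample size arithmetic is not at fault.

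**What to change.** Amend sections 8.6 and 10 to:

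1. State one common horizon for all randomised patients, for deterioration and for death (day 28 is an example).
2. Keep patients discharged alive in the risk set as event-free to that day.
3. Make the comparison of cumulative incidence or proportions primary, reported as a risk difference with 95% confidence interval, and give the cause-specific hazard ratio as supportive.
4. Tie the 25% and 10% in section 4.4 to the same horizon.

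For the in-hospital endpoint this needs no new data. A day-28 record check for deaths and ICU readmission after discharge is optional. If it is added, the protocol should say that it widens the endpoint.

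The cost is an amendment and a little more analysis work. Power is slightly lower if treatment leaves discharge unaffected (83% against 87% in the model above). Patients with no later information are assumed event-free after discharge.
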